## Abstract

**Methods:**

A total of *N* = 44 parents with elevated parenting stress and raising children aged 4 to 14 years will be recruited. Participants will be randomly assigned in a 1:1 ratio to either the treatment immediate group (TI) or a waitlist control group (WL). Primary outcomes will include participant's parenting stress and other parenting-related correlates (e.g., parental mentalizing, personality functioning, self-efficacy, and mental health, parent-child relationship quality), and children's variables (e.g., child's behavior difficulties and temperament). Parents' subjective experiences and satisfaction with the intervention will also be assessed. Secondary outcomes will include recruitment, retention, and dropout rates, as well as participant characteristics and factors influencing intervention effectiveness. The data will be analyzed qualitatively and quantitatively.

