### Primary research questions

To evaluate the potential efficacy of the randomized controlled trial (RCT), the primary research questions focus on changes in parenting stress:

Do parents in the TI group report a greater reduction in parenting stress index (PSI) scores following the 5-week intervention, compared to those in the WL group?

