### Secondary research questions

Firstly, to more comprehensively investigate the mechanisms through which the LPP alleviates parenting stress, additional correlates related to parents, children, and the parent–child relationship, as well as participants' experiences with and satisfaction toward the program, are assessed before and after the intervention. Secondly, in the context of implementing the LPP in China, exploratory questions arise regarding its preliminary feasibility and practical applicability. On this basis, the present study is designed to address the following secondary research questions:

Do parents in the TI group report greater improvements in parenting-related correlates—including parental reflectivity, self-efficacy, mental health, and the quality of the parent-child relationship—compared to the WL group following the 5-week intervention?Do parents in the TI group report greater improvements in child outcomes, specifically reductions in behavioral difficulties and positive changes in temperament (e.g., emotionality), compared to the WL group post-intervention?How do parents subjectively experience their participation in the LPP?What is the overall level of participant satisfaction with the intervention program?What are the recruitment rates?What are the characteristics of study enrollees and participants?What are the retention, dropout, and compliance rates?What are the reasons for participant dropout?What factors might be associated with the retention and effectiveness of the intervention?

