## Measures

### Primary outcomes

#### Parenting stress

The parenting stress index/short form (PSI/SF; Abidin, 1986) assesses self-reported PS with 36 items. Items are rated on a five-point Likert scale from 1 (strongly disagree) to 5 (strongly agree). The Chinese version is consistent with the original structure and the internal consistency of Chinese version of the total scale was 0.93, with 0.85 for Parental Distress scale, 0.86 for Parent-Child Dysfunctional Interaction scale, and 0.87 for Difficult Child scale (Ren, 1995).

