### Secondary outcomes

(1) Additional parent-, child-, and parent–child relationship-related correlates.

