### Statistical analysis

All parents assessed at baseline (T0) will be included in the data analysis following intent-to-treat principles. Sociodemographic variables and baseline assessment data will be used to characterize the enrolled sample. Descriptive data on recruitment, dropout, and retention rates will also be collected. Additionally, qualitative data—including reasons for dropout—will be analyzed to evaluate the appropriateness and acceptability of the study procedures and intervention. The primary objective of this study is to examine changes in participant's parenting stress and other parenting-related correlates (e.g., parental mentalizing, personality functioning, self-efficacy, and mental health), parent-child relationship quality, and children's variables (e.g., child's behavior difficulties and temperament) before and after the intervention, measured by standardized questionnaires. Participant satisfaction will be assessed using a standardized questionnaire. Furthermore, parents' subjective experiences during the LPP will be explored through semi-structured interviews. The quantitative data will be analyzed using SPSS 21.0 (IBM Corp., Armonk, NY, USA), employing repeated measures ANOVA (rmANOVA), *t*-tests, and chi-squared tests. The analysis of qualitative data will be conducted using the grounded theory methodology.

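### The abstract and the stated primary objective cover eight constructs, while the research questions, sample size and measures make parenting stress the only primary outcome

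*Protocol article*

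**What the plan says.** The protocol article ranks its outcomes in two ways.

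**Broad hierarchy**
- Abstract, Methods: "Primary outcomes will include participant's parenting stress and other parenting-related correlates". The constructs named are parenting stress, parental mentalizing, personality functioning, self-efficacy, mental health, parent-child relationship quality, child behavior difficulties and child temperament. The lists are given as examples, so they are open-ended.
- Same paragraph: "Secondary outcomes will include recruitment, retention, and dropout rates", followed by participant characteristics and factors that influence effectiveness. No clinical scale is secondary here.
- Statistical analysis: "The primary objective of this study is to examine changes in participant's parenting stress and other parenting-related correlates", continuing through the same eight constructs.

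**Narrow hierarchy**
- Primary research questions: "the primary research questions focus on changes in parenting stress". One question follows, on PSI scores.
- Measures, Primary outcomes: the PSI/SF is the only instrument described ("assesses self-reported PS with 36 items").
- Sample size: the expected changes are for PSI total stress and no other measure.
- Secondary research questions: "Do parents in the TI group report greater improvements in parenting-related correlates", with a further question on child outcomes.
- Measures, Secondary outcomes: the first group is headed "Additional parent-, child-, and parent–child relationship-related correlates", and the seven remaining constructs are described beneath it.

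**The concern.** The same seven constructs are primary in one part of the article and secondary in another, and no sentence reconciles the two. A primary outcome is fixed in advance so that one result can be recognised as the planned test whatever the data show. If PSI shows no difference and, say, self-efficacy does, the abstract would allow the second result to be reported as a primary finding, while the Measures section would not. In a trial of 44 parents with self-reported scales, a chance difference on one of eight constructs is quite possible, so the choice of hierarchy affects how the result is read.

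**Working it through.** **1. Side-by-side comparison**

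| Construct | Abstract | Statistical analysis (primary objective) | Research questions | Measures | Sample size basis |
|---|---|---|---|---|---|
| Parenting stress (PSI) | primary | included | primary | primary | yes |
| Parental mentalizing | primary | included | secondary | secondary | no |
| Personality functioning | primary | included | not named | secondary | no |
| Self-efficacy | primary | included | secondary | secondary | no |
| Parental mental health | primary | included | secondary | secondary | no |
| Parent-child relationship | primary | included | secondary | secondary | no |
| Child behavior difficulties | primary | included | secondary | secondary | no |
| Child temperament | primary | included | secondary | secondary | no |

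Seven of the eight rows conflict. This step needs no assumption.

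**2. The plan's own figure**

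Inputs from the Sample size section: PSI decreases of 11.3 and 3.1, alpha 0.1, power 0.8, 20 per group, 10% attrition, 44 in total.
- Attrition step: 20 × 1.1 = 22 per group, and 2 × 22 = 44. This reproduces. Dividing by 0.9 would give 23 per group.
- The 20 per group cannot be reproduced, because no standard deviation is given and the sidedness and the scale of the 10% margin are unclear.
- Ignoring the margin, the SD that would give 20 per group is SD = δ·√(n/2)/(z_α + z_power), with δ = 11.3 − 3.1 = 8.2:
  - one-sided 0.10: 8.2 × √10/(1.282 + 0.842) = 12.2
  - two-sided 0.10: 8.2 × √10/(1.645 + 0.842) = 10.4

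**3. False-positive chance if all eight are treated as primary**

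Assumption: eight separate unadjusted tests with no true effect on any of them. For independent tests the chance of at least one false positive is 1 − (1 − α)^8.
- α = 0.05: 1 − 0.95^8 = 0.337
- α = 0.10: 1 − 0.90^8 = 0.570

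Scales completed by one parent are likely to be correlated. Simulating eight equally correlated two-sided z-tests (400,000 draws) gives:

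| Assumed correlation | α = 0.05 | α = 0.10 |
|---|---|---|
| 0 | 34% | 57% |
| 0.3 | 30% | 51% |
| 0.5 | 25% | 44% |
| 0.7 | 19% | 34% |

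With PSI as the only primary outcome, the figure is the nominal 5% or 10%.

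**4. Which hierarchy the design can support**

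Suppose eight co-equal primaries were intended, with Bonferroni control from 0.10, so 0.10/8 = 0.0125 each, two-sided. Power for PSI at 20 per group is Φ(δ/(SD·√(2/20)) − 2.498):
- SD 12.2: Φ(2.123 − 2.498) = 0.35
- SD 10.4: Φ(2.486 − 2.498) = 0.50

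Reaching 80% would take about 50 or 37 per group respectively. These figures rest on the back-solved SDs. They indicate that the stated sample size fits a single PSI primary and not eight adjusted ones.

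**The case against.** The best defence is that the design sections agree. The primary research question, the sample size and the Measures section all single out PSI, so a careful reader can work out the intended primary outcome. The abstract is the only place that calls the other constructs primary outcomes. The Statistical analysis section speaks of a primary objective of examining changes, which does not designate endpoints or tests. The trial also describes itself as exploratory and a pilot, with findings of preliminary value only.

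Much of this stands, and it limits the consequence. A reader might infer that the plan lets success be declared on any one of many tests. The article does not support that: it states no success rule and no order of testing. A reader might also count the lack of a multiplicity adjustment as a fault. The statistical analysis plan is not shown and could contain one, so its absence from the article is not a finding. Nor should 57% be quoted alone: alpha 0.1 is stated only for sample size estimation, and independence is the extreme case for scales from one respondent.

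The defence does not remove the contradiction. Condensing a protocol into an abstract drops detail, but here seven constructs change rank and the secondary outcomes are redefined. The same list recurs in the main text as the primary objective. An analysis plan could settle the testing but would leave the article contradicting itself. An exploratory trial that poses a comparative question and sizes itself at 80% power still needs one identifiable primary outcome.

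**Conclusion.** The point holds as an internal contradiction. The abstract's primary outcomes and the primary objective cover eight constructs. The primary research question, the sample size basis and the Measures section single out PSI, and the remaining seven constructs are secondary in Measures, six of them also in the secondary research questions. The better-supported reading is that PSI is the only primary outcome.

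The consequence is conditional. The broader wording does not exclude treating any of eight constructs as a primary result. If that were done with separate unadjusted tests, the chance of at least one false positive would be several times the nominal level, as tabulated above. Those figures depend on assumed correlations and on a significance level that the article does not set for the analysis. The contradiction depends on neither.

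**What to change.** Reword two places in the protocol article:
- **Abstract, Methods:** name the PSI-SF total score as the single primary outcome, compared between the immediate-treatment and waitlist groups at T1. Move the other seven constructs to the secondary outcomes, beside the feasibility measures.
- **Statistical analysis:** restrict the primary objective to that same comparison, and describe changes in the other constructs as secondary objectives.

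PSI as the primary outcome comes from the primary research question and from Measures, and the use of the total score comes from the Sample size section. T1 comes from Data collection procedure, where it is the assessment of both groups before the waitlist group is treated. Label all other scales and the PSI subscales secondary or exploratory, in line with the secondary research questions and the Secondary outcomes heading.

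The cost is a few sentences. No measure, visit, participant or analysis is added. The change should be made before outcome data are examined, so that the choice of primary outcome cannot depend on the results.

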**Discussion:**

This study signifies the first implementation of LPP in Asia, emphasizing prevention. It seeks not only to evaluate the clinical utility of LPP but also to initially explore the implementation potential of MBT-based prevention programs in China. Findings from this trial are expected to inform future directions in the development and implementation of culturally attuned psychotherapeutic interventions in China.

**Clinical trial registration:**

clinicaltrials.govclinicaltrials.gov, identifier: NCT06858059.

## Introduction

Emerging evidence suggests that the period before age 14 represents a critical window for the prevention of mental health difficulties (Kessler et al., 2005). Despite this, systematic approaches to identifying at-risk children and delivering timely, targeted interventions remain limited in routine clinical practice (Plueck et al., 2010; Heinrichs et al., 2005; Bolinski et al., 2022). Behavioral problems in children with such risks often emerge early and exert a significant burden on parenting. These difficulties frequently elicit high levels of parenting stress. Developmentally, children in this age group are typically not equipped to seek support autonomously, underscoring the importance of facilitating intervention access through parents. Enhancing parental access to support thus represents a critical strategy for the timely prevention of early mental health issues.

Moreover, it has been found that caregivers' own psychological vulnerabilities and parenting-related correlates are not only strongly associated with children's early mental health problems, related behavioral problems, and competence development through parenting stress (Ribas et al., 2024), but also frequently engage in a vicious cycle: children of parents with high levels of parenting stress are at greater risk of developing such problems, which in turn further elevate the parents' parenting stress (Evers et al., 2023; Cherry et al., 2019; Dijk et al., 2022; Daundasekara et al., 2021; Huang et al., 2025; Kochanova et al., 2022). Moreover, the association between children's externalizing behaviors—such as emotion dysregulation, aggression, and attention problems—and parenting stress is significantly stronger than that observed with internalizing problems, thereby positioning externalizing behavior problems as a more salient influencing factor within this dynamic (Cooke et al., 2019; Williford et al., 2007).

Existing research on parenting stress among Chinese parents remains limited. Preliminary evidence indicates that parents report high levels of stress stemming from time constraints, unmet guidance needs and work–life conflicts (Department of Chinese Women Children's Federation, 2023; Bian et al., 2022; Qian et al., 2021; Lau and Power, 2020). The influence of parenting stress on parenting behavior is also evident in Chinese families, manifesting as harsh discipline (Niu et al., 2018). Furthermore, paternal parenting stress has been found to positively predict parental burnout and children's emotional–behavioral problems (Yue et al., 2025), whereas higher parenting self-efficacy is associated with a lower likelihood of falling into high-stress groups (Wang and Cheng, 2025). Collectively, these findings suggest that Chinese parents lack effective and contextually appropriate parenting strategies, underscoring a pressing need for targeted interventions. However, relevant intervention programs remain scarce (Qu et al., 2024). In this context, introducing well-established programs from other regions represents a viable first step toward addressing this practical gap.

Parent-focused interventions have shown preliminary efficacy in reducing parenting stress, enhancing parental wellbeing, and improving parenting behaviors—including reduced harsh discipline or coercive parenting practices and increased positive discipline and encouragement. These improvements may, in turn, contribute to a reduction in parent–child conflict. Furthermore, children's externalizing problems (e.g., aggression, hyperactivity) and internalizing problems (e.g., anxiety, depression) are reduced (Bjørknes and Manger, 2013; Gervinskaite-Paulaitiene et al., 2023; Scott et al., 2014). Based on these findings, researchers have continued to investigate potential “meta-factors” that may influence this process. Among various mechanisms of change, the enhancement of parental reflective functioning and mentalizing capacity has garnered significant attention and is recognized as a core mechanism linking parent-level improvements to child behavioral outcomes (Barlow et al., 2021; Lavender et al., 2023; Nieto-Retuerto et al., 2024). This improvement is particularly marked within the domain of mentalization-based parenting interventions.

Mentalization-based therapy (MBT), widely used in reducing personality disorder symptomatology (Luyten et al., 2020), has demonstrated increasing relevance in prevention in the parenting context (Byrne et al., 2020; Sadler et al., 2013; Sleed et al., 2013). Initial evidence supports the assumption that an increased parental understanding of their own and their children's internal states, fosters more adaptive and sensitive caregiving responses in parental challenges and improves parent–child relationships (Barlow et al., 2021). MBT is also thought to reduce the intergenerational transmission of maladaptive attachment patterns (Midgley, 2024). Conversely, MBT remains relatively novel and underexplored within the Chinese context. To date, only one published study has examined its application, specifically evaluating mentalization-based family therapy (MBFT) combined with mindfulness therapy to reduce suicidal ideation in adolescents (aged 12–18) with depressive disorders in a hospital setting (Fan et al., 2024).

By contrast, MBT has already been implemented relatively widely in other regions. The lighthouse parenting programme (LPP; Byrne et al., 2015) is currently one of the most widely implemented MBT parenting intervention and has to date been adopted across multiple countries in Europe and South America (Byrne et al., 2019; Volkert et al., 2022; Hestbaek et al., 2026; Gervinskaite-Paulaitiene et al., 2023; Costa-Cordella et al., 2025). With a strong emphasis on attachment theory and child development, LPP explicitly targets parental reflective functioning, promotes epistemic trust, and aims to support parents in exploring their own emotional experiences while responding to their children's needs. Initial evidence supports the assumption with observed changes in a range of domains, including reductions in child maltreatment, coercive parenting, parenting stress, and child behavioral problems, along with improvements in parental mental health, family relationships, parental teamwork, self-efficacy, self-focused mentalizing, and parenting conditions of parents with psychological disorders (Byrne et al., 2019; Gervinskaite-Paulaitiene et al., 2024; Byrne, 2020; Hestbaek et al., 2025). However, these preliminary findings are predominantly derived from pilot investigations or pre–post designs, often characterized by limited sample sizes and constrained statistical power. To date, randomized controlled trials evaluating the effectiveness of the LPP remain limited. Existing evidence consists of an RCT of the 20-week LPP conducted in England, along with a cluster of related trials in Germany—most notably, an RCT of the 5-week LPP carried out within the UBICA project (Neukel et al., 2021; Sleed et al., 2023; Herpertz et al., 2025). Furthermore, its application and empirical evaluation within Asian populations remain entirely absent from the extant literature.

Despite its promise, LPP has yet to be evaluated in non-Western cultural contexts. As the first application of the LPP in Asia, this study addresses a significant gap in research on interventions for parents experiencing elevated parenting stress. In terms of efficacy, the study will explore the extent to which the LPP may influence on parents' self-assessed results of participant's parenting stress and other parenting-related correlates (e.g., parental mentalizing, personality functioning, self-efficacy, and mental health), parent-child relationship quality, and children's variables (e.g., child's behavior difficulties and temperament), alongside parents' subjective experiences and satisfaction with the program. These outcomes, particularly the qualitative findings, will inform the ongoing refinement of the LPP with respect to its cultural relevance and applicability within Eastern contexts.

Additionally, as the first prevention program for parents with elevated parenting stress in China, the study will evaluate the applicability of LPP implementation. This includes examining recruitment rates, participant characteristics, retention, dropout, and adherence, as well as reasons for attrition and possible variables that might be associated with intervention effectiveness. The findings aim to inform the development of scalable, context-sensitive early intervention strategies for preventing child mental health difficulties in China.

### Primary research questions

To evaluate the potential efficacy of the randomized controlled trial (RCT), the primary research questions focus on changes in parenting stress:

Do parents in the TI group report a greater reduction in parenting stress index (PSI) scores following the 5-week intervention, compared to those in the WL group?

### Secondary research questions

Firstly, to more comprehensively investigate the mechanisms through which the LPP alleviates parenting stress, additional correlates related to parents, children, and the parent–child relationship, as well as participants' experiences with and satisfaction toward the program, are assessed before and after the intervention. Secondly, in the context of implementing the LPP in China, exploratory questions arise regarding its preliminary feasibility and practical applicability. On this basis, the present study is designed to address the following secondary research questions:

Do parents in the TI group report greater improvements in parenting-related correlates—including parental reflectivity, self-efficacy, mental health, and the quality of the parent-child relationship—compared to the WL group following the 5-week intervention?Do parents in the TI group report greater improvements in child outcomes, specifically reductions in behavioral difficulties and positive changes in temperament (e.g., emotionality), compared to the WL group post-intervention?How do parents subjectively experience their participation in the LPP?What is the overall level of participant satisfaction with the intervention program?What are the recruitment rates?What are the characteristics of study enrollees and participants?What are the retention, dropout, and compliance rates?What are the reasons for participant dropout?What factors might be associated with the retention and effectiveness of the intervention?

